#### Temperament, sleep, and eating behaviour

Between-group differences would be useful to study mediation or moderation of effect and to assess any adverse effects of our intervention on temperament and sleep.

#### Psychological mediators of infant-feeding behaviours

Differences in maternal attitudes, beliefs, intentions, self-efficacy, and outcome expectancies will be assessed between intervention and control groups. Mediation analyses will be conducted to examine to what extent any effect of the intervention on infant feeding behaviours is fully or partially explained by the above beliefs.

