Infancy is a period of rapid growth and could be a critical time when obesity prevention may be most effective. Recent systematic reviews have described a consistent association between rapid weight gain in infancy and subsequent obesity risk in childhood and later life [8–10]. Energy deposition as a percentage of total energy requirements decreases from 40 % at 1 month to 1 to 2 % from 12 months until mid-adolescence. Therefore, infancy weight gain is more closely related to energy intake, than is weight gain in childhood or in later life. In 2004, based on new data on energy expenditure in infants, the World Health Organisation (WHO) reduced the recommended energy requirements for infants by 15 to 20 % [11]. Current formula-feeding instructions in UK are based on the previous 1985 WHO recommendations and this may be an important reason why formula-fed babies are at a greater risk of rapid weight gain and subsequent obesity than breastfed infants. Three meta-analyses of observational studies reported that obesity risk at school age was reduced by 15–20 % in breastfed compared with formula-fed infants [12–14]. In 2006, the WHO published growth charts based on the growth of breastfed babies and recommends this lower plane of growth as the optimum standard for growth of all infants [15, 16]. While the benefits of breastfeeding are well recognised, the 2010 UK Infant Feeding Survey showed that only 21 % of babies were exclusively breastfed at age 6 weeks and 1 % at 6 months [17]. Hence in addition to supporting breastfeeding, it is important to optimise the growth of formula-fed babies.

In the *Baby Milk* trial we aim to evaluate the efficacy, cost-effectiveness and acceptability of a theory-based, multi-component intervention to reduce formula-milk intake (based on the 2004 WHO recommendations for energy requirements) and prevent excess weight gain during infancy. We also aim to understand the psychological mediators of any effect of the intervention on formula-milk and energy intake.

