### Measurements

A summary of the measurements undertaken is presented in Table 1.

**Table 1 Tab1:** Study measures

Measures	Baseline	4 months	6 months	8 months	12 months
Questionnaire measures					
Baseline questionnaire^a^	I, C				
Milk feeds questionnaire	I, C	I, C	I, C		
Maternal attitudes^b^	I, C		I, C		
Temperament, sleep and eating behaviour^c^			I, C		
4-day diet diary^d^				I, C	
Health Service Utilisation			I,C		I, C
Maternal quality of life^e^	I, C		I,C		I,C
Maternal anxiety^f^	I, C		I,C		
Intervention evaluation			I		I
Anthropometry					
Parents’ height	I, C				
Parents’ weight	I, C		I, C		I, C
Baby weight	I, C	I	I, C		I, C
Baby supine length	I, C	I	I, C		I, C
Baby head circumference	I, C		I, C		I, C
Baby abdominal circumference	I, C		I, C		I, C
Baby skin fold thickness					I, C
Baby abdominal Ultrasound					I, C

*I* Intervention group; *C* Control group

^a^Baseline Questionnaire: Parents: Demography (age; education - age at completion and highest qualification; occupation; ethnicity; marital status - cohabiting/married/single); weight and height. Mother’s: lifestyle (smoking - during pregnancy, current alcohol consumption), pregnancy (duration, weight -before pregnancy and at time of delivery), delivery (normal, instrumental, or caesarean) and previous children (number, feeding-breast, formula, dependent on instructions/appetite/growth - Likert scale). Baby’s: sex, weight and length at birth and 6 weeks

^b^Maternal attitudes and feeding practices (questionnaire developed for use in this study): Mother’s attitudes; psychological measures based on Social Cognitive Theory (self-efficacy, outcome expectancy, intentions, and motivation); perception of baby’s weight. Type of feed (breast/ expressed/ formula/ mixed), feed on demand/routine/both; feed based on instructions/appetite/growth – Likert scale

Bottle feeds (type, frequency, amounts, duration, how reconstituted, advice followed, age when started), Breastfeeds (frequency, duration, and expressed milk). Other drinks and foods. Age at weaning (only at 6 months)

^c^Validated questionnaires used with permission from [name] and [name]

^d^Diet diary: developed in collaboration with MRC HNR, and used in the National Diet and Nutrition Survey of Infants and Young Children

^e^Quality of Life: EuroQol Visual Analogue Scale and Short Form 8

^f^Anxiety: Spiegelberger Short State Anxiety Inventory

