#### Questionnaires

A baseline questionnaire will be used to collect data from parents about demography (age, education, occupation, ethnicity, marital status), lifestyle (smoking, alcohol consumption, BMI), pregnancy (duration, weight gain), delivery and previous children (number, feeding).

We have developed and validated a questionnaire to assess milk feeding practices and hypothesised psychological mediators of any intervention effect informed by Social Cognitive Theory: attitudes, self-efficacy, outcome-expectancies and intentions with regard to following feeding recommendation (feeding and growth questionnaire) [18]. Baby eating behaviour, sleep and temperament have recently been studied as potential risk factors for obesity [19–21]. We will use a combination of questionnaires developed by other groups ([name] and [name]) to assess these. The temperament questionnaire has been validated for use in infants [22] and the eating behaviour questionnaire has been validated in older children [23, 24].

A 4-day diet diary will be used to assess energy intake at 8 months. The diary will be the same as that used by the MRC Human Nutrition Research Unit (MRC HNR) for the National Diet and Nutrition Survey of Infants and Young Children (DNSIYC). Dietary data will be analysed using the Diet in Nutrients Out (DINO) computer package [25] by the dietary assessment team at the MRC HNR, who will not be aware of group allocation.

Parent’s quality of life will be assessed using the EuroQoL Visual Analogue Scale (VAS) and Standard Form (SF) 8. A questionnaire to measure health service utilisation (hospital, primary and community care use) using standard questions will be administered at 6 and 12 months. Parents’ perceptions of the usefulness of the different components of the intervention (face-to-face and telephone contacts, leaflets, stickers) will be assessed among intervention group participants.

The questionnaires will be self-administered prior to the visit with an opportunity to clarify any doubts during the visit.

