#### Dietary intake

Differences in milk intake between intervention and control groups at 2, 3, 4, 5 and 6 months and age at introduction of solids will be compared using questionnaire data. Energy intake from 4-day diet diary data will be compared at 8 months.

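### Beliefs are measured after randomisation only at 6 months, so the mediation analysis cannot tell whether beliefs changed formula intake or formula intake changed beliefs

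*Protocol article*

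**What the plan says.** The Background makes mediation a stated aim and names two outcomes: "We also aim to understand the psychological mediators of any effect of the intervention on formula-milk and energy intake". The Data analysis subsection on psychological mediators then makes this promise, with maternal beliefs as the explanation: "Mediation analyses will be conducted to examine to what extent any effect of the intervention on infant feeding behaviours is fully or partially explained". It does not say which feeding measure is paired with which belief measure.

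The belief instrument appears in Table 1 as the maternal attitudes row, whose footnote lists "psychological measures based on Social Cognitive Theory (self-efficacy, outcome expectancy, intentions, and motivation". That row has entries for both arms at baseline and at 6 months, and its 4-month cell is empty. The milk feeds questionnaire is scheduled for both arms at baseline, 4 and 6 months.

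The Dietary intake subsection compares "Differences in milk intake between intervention and control groups at 2, 3, 4, 5 and 6 months", and compares diary energy intake at 8 months. The Questionnaires subsection describes feeding practices and mediators as parts of one instrument: "We have developed and validated a questionnaire to assess milk feeding practices and hypothesised psychological mediators of any intervention effect".

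**The concern.** A mediator has to change before the outcome that it is said to explain. Here the only belief score that can carry an intervention effect is collected when most of the formula intake has already happened.

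The reverse path is plausible in this trial. Intervention parents check feeds against guideline amounts and receive feedback on growth. A mother whose baby settles on smaller feeds may report higher self-efficacy for that reason. A standard mediation model would read the resulting correlation as beliefs driving intake.

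At stake is the conclusion on a stated aim: a claim that beliefs explain all or part of the effect on formula intake would have no support in the design. The primary comparison of weight gain is not affected.

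**Working it through.** **1. Order of measurement.** Only participants who attend the baseline visit are randomised (Randomisation and consent), so the baseline belief score cannot reflect the intervention. That leaves the 6-month score.

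| Feeding outcome | Position relative to 6-month beliefs |
|---|---|
| Formula intake at 2, 3, 4, 5 months | before |
| Formula intake at 6 months | same occasion |
| Diary energy intake at 8 months | after |

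No formula-intake comparison follows the post-randomisation mediator.

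**2. Inputs for the size.** The protocol gives no figure for false mediation, so there is none to reproduce.
- Infants per arm: 270, the middle of the stated 250 to 290.
- Intake effect: the sample size section powers on a 10 % to 11 % reduction from 2768 kJ/day. That is 0.10 × 2768 = 277 and 0.11 × 2768 = 304 kJ/day. Divided by the SD of 479, this is 0.58 to 0.64 SD. I use 0.6 SD, and 0.3 SD as an assumed lower case.
- Assumed, not in the protocol: a reverse path *g* from intake to beliefs (SD per SD) of 0 to 0.5, belief stability of 0.5 from baseline, and intake persistence of 0.6 between visits.

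**3. Apparent share mediated when true mediation is zero.** Let intake be *Y* = −*dT* + *e*, with *T* the treatment arm and Var(*e*) = 1, and let beliefs depend on intake only through −*gY*. Belief variance given arm and baseline beliefs is 1 − 0.5² = 0.75.
- Arm to beliefs: *a* = *g* × *d*.
- Beliefs to 6-month intake, given arm: *b* = −*g* / 0.75.
- Apparent share: *ab* / (−*d*) = *g*² / 0.75. At *g* = 0.3 this is 0.09 / 0.75 = 12 %. At 0.5 it is 0.25 / 0.75 = 33 %.
- For 4-month intake, multiply by the persistence of 0.6: 7 % and 20 %.

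**4. How often mediation is falsely declared.** The test requires both paths to be significant at the two-sided 5 % level. For *g* of 0.3 or more, path *b* is almost always significant, so path *a* decides. Its standard error is √(2 × 0.75 / 270) = 0.0745.

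| *g* | *d* | *a* / SE | Rate, Φ(*a*/SE − 1.96) |
|---|---|---|---|
| 0.3 | 0.3 | 0.09 / 0.0745 = 1.21 | 23 % |
| 0.3 | 0.6 | 0.18 / 0.0745 = 2.42 | 68 % |
| 0.5 | 0.3 | 0.15 / 0.0745 = 2.01 | 52 % |
| 0.5 | 0.6 | 0.30 / 0.0745 = 4.03 | 98 % |

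Simulation at 270 per arm gives about 24-69 % at *g* = 0.3 and 46-96 % at 0.5. At *g* = 0.1 it gives about 3-10 %, and with no reverse path under 1 %. The formula and the simulation agree to within a few points; the exact rate moves with the belief variance assumed. Adjusting for baseline beliefs does not prevent the problem.

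**5. Does moving to the 8-month outcome cure it?** Not alone. If 6-month intake drives 6-month beliefs and also predicts 8-month intake, the reverse path passes through. By the formula in step 3, the apparent share is again 0.6 × *g*² / 0.75, or 7 % and 20 %. In simulation with *g* from 0.3 to 0.5, adjusting only for baseline values still gave false mediation in 24-96 % of trials. Adding 6-month intake as a covariate cut this to about 1-6 %.

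**The case against.** The protocol fixes no estimator, outcome time or covariates for mediation. Those commonly go to an analysis plan, which is not shown. That stands as a limit on what can be said about the model, but not on the main point: the schedule is fixed in Table 1, and no analysis plan can supply a belief measure between randomisation and 6 months.

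The percentages rest on a reverse path for which the protocol gives no value, and they fall to almost nothing when it is zero. That stands too. They are illustrations and not forecasts.

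Mediation is also explanatory. The intention-to-treat comparison, the safety monitoring and the simple comparison of beliefs between arms are unaffected, and the planned interviews on feeding decisions give separate insight. Measuring mediators at the end of an intervention is a recognised compromise to limit questionnaire burden.

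A reader might infer that the whole mediation aim fails. The documents do not support that, because the aim also names energy intake and the 8-month diary follows the belief measure. A reader might also infer that restricting the outcome to 8 months is enough. Step 5 of the working shows that it is not, if intake persists between visits.

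**Conclusion.** The point holds for formula intake from 2 to 6 months. Its effect precedes or coincides with its supposed cause, so the data cannot distinguish the two directions. That conclusion follows from the schedule and needs no assumed value.

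The size of the error does need assumptions: it runs from under 1 % false claims with no reverse effect to 46-96 % at a path of 0.5, for intake effects of 0.3 to 0.6 SD. By date, the ordering fault does not extend to 8-month energy intake, although that analysis needs adjustment for 6-month intake. The change should be made because it is cheap and protects a stated aim; nothing in the primary analysis depends on it.

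**What to change.** In the subsection on psychological mediators:

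- Make no causal claim that beliefs explain, in full or in part, the effect on 2- to 6-month formula intake. Report those results as associations.
- Name 8-month diary energy intake as the mediation outcome. Adjust for baseline beliefs, baseline milk intake and 6-month milk intake, and report the indirect effect with a bootstrap interval.
- Optionally, add the belief items to the 4-month milk feeds questionnaire, which both arms already receive, for infants still to reach 4 months. Use 4-month beliefs for 6-month intake, adjusted for baseline beliefs, baseline intake and 4-month intake. The article says that the trial was recruiting at submission, so this would reach later enrolees only.

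The first two changes cost only wording. The third costs a slightly longer form and an amendment. The mediation claim becomes narrower. It also becomes less precise, because adjusting for intake at the time beliefs are measured captures only the later part of any mediated effect.

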#### Parents’ anthropometry

A useful halo-effect of our intervention would be if due to increased awareness, parents lost weight. At 12 months, we will compare parents’ BMI between intervention and control groups, adjusted for baseline measures.

#### Acceptability

Parents’ satisfaction with different aspects of the intervention will be assessed at 6 months using a questionnaire. Semi-structured interviews in a sub-sample of intervention and control group participants and all facilitators will explore how feeding decisions were made, to explain any intervention effects, identify which components were acceptable and potentially effective, how participants responded to the intervention or control contacts, any contextual factors that influenced participant responses, and barriers and facilitators of intervention delivery as perceived.

#### Costs, health service utilisation, and economic analysis

We developed instruments to collect facilitator time spent in delivering the intervention and infant primary and secondary health service utilisation. The total cost of the intervention from the perspective of the NHS will be determined by multiplying these quantities by nationally representative unit costs. The economic evaluation will comprise a cost-consequences analysis to show the cost of delivering the intervention plus infant health service costs and outcomes (proportion of infants whose weight crosses more than one centile band upwards on the growth charts (0.67 SDS), infants of normal weight at 12 months, and probability of being normal weight as an adult using data from a meta-analysis [39]), for intervention and control groups. Where appropriate, incremental cost-effectiveness ratios will also be calculated, and uncertainty presented as 95 % confidence intervals around incremental costs and outcomes, and cost-effectiveness acceptability curves.

### Confidentiality

All information that is collected will be kept strictly confidential and stored anonymously, using a study identification (ID) number, by the MRC Epidemiology Unit, University of Cambridge and its collaborators, which includes the University of East Anglia. Codes connecting individual identity to the stored data records will be kept separately. The database containing personal information will be stored on a password and firewall protected secure standalone server, in the MRC Epidemiology Unit, University of Cambridge.

### Assessment of safety

As the aim of the intervention is to realign the growth of formula-fed infants more closely to that of breastfed infants, we consider that the risks to the babies (and parents) will be negligible. However we will actively elicit and record any (seemingly related or unrelated) adverse events and report/take action as appropriate.

#### Eliciting adverse events

Baby weight measurements might reveal underweight (weight <0.4^th^ centile) or weight faltering (crossing down through ≥2 weight centile lines). We will also ask at each visit whether the baby has had any unplanned contacts with a health professional (that is, other than routine immunisations or health checks) and ask the parent/caregiver if they have any health concerns about the baby. A potential unintended consequence of the Baby Milk intervention could be increased anxiety for the parent(s). Changes in anxiety levels will be assessed using the EuroQoL Visual Analogue Scale (VAS), completed by the primary caregiver (usually the mother) at baseline and 6-month visits. A drop in score of >30 points at 6 months will initiate a follow-up phone call by the study team.

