The intervention will be delivered by trained facilitators (research nurses) from the baby’s enrolment in the trial (2 to 14 weeks old) to 6 months and will consist of three face-to-face sessions and two telephone contacts in addition to two leaflets based on SCT (Fig. 1). The face-to-face sessions will last approximately 30 to 45 min and the telephone contacts 15 to 20 min. Since social support is important, both parents will be encouraged to attend the face-to-face sessions. During the first session, the facilitator will talk parents through the ‘healthy infant growth and nutrition’ leaflet that explains the new feeding recommendations (Table 2) and the growth charts. The leaflet does not just impart knowledge about amounts of formula-feeds, hunger cues, growth charts and rapid weight gain, but also aims to encourage recommended feeding behaviours by strengthening self-efficacy and perceived benefits about following the recommendations. Demonstration of correct feed preparation (if required) and explanation of the feeding recommendations will be provided. Parents will be encouraged to make a feeding plan and provided with stickers to put on the formula milk packets. When the baby is 4-months old, parents will be invited for a second session and advice on weaning and feedback on baby’s growth will be provided. Two phone-calls - when the baby is age 2 to 3 months and 5 months - will be made to monitor progress with following recommendations and to support the parents with ongoing goal setting, action planning, self-monitoring and problem-solving. At the 6-month visit, the baby’s growth will be plotted on the WHO growth charts. Facilitators will feed back this information to parents, and they will be encouraged to monitor the growth of their babies also after the end of the intervention delivery at 6 months. Growth monitoring is important because parents are not very good at identifying obesity in their children [36], so any programme to prevent obesity must include early identification.

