### Control group

The control group will be offered the same number of contacts with facilitators (attention control) and general information about formula-feeding (bottles, teats, sterilisation, making up feeds) will be discussed. The 4 to 6 weekly phone calls will be used to discuss general issues (parenting, sleep, etcetera), to monitor feed quantity and frequency and to encourage continued participation in the study.

Parents in both groups will be given a help-line number to contact the study team about feeding issues.

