#### Growth

Weight, length and BMI will be converted to SDS adjusted for age and sex using the British 1990 growth reference and the WHO 2006 growth standard at different time points (birth, baseline, six and 12 months). Babies in the intervention and control groups will be compared for change in weight, length and BMI SDS from birth and baseline to 6 and 12 months. Percentage of babies crossing the 1 percentile band (0.67 SDS) in the two groups will be compared. Their abdominal circumference, sub-cutaneous and intra-abdominal fat (skin-fold thickness and ultrasound measurements) will also be compared at 1 year.

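### Babies are weighed at 4 months in the intervention arm only, so any by-arm count of underweight or weight faltering is expected to be higher there even with no true effect

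*Protocol article*

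**What the plan says.** **Schedule.** The baby-weight row of Table 1 (Measurements) reads "Baby weight I, C I I, C I, C", where I and C are defined as "Intervention group; *C* Control group". The columns are baseline, 4, 6, 8 and 12 months, and the 8-month cell is empty. Weight is therefore taken in both arms at baseline, 6 and 12 months, and in the intervention arm alone at 4 months. Supine length follows the same pattern. The milk feeds questionnaire in the same 4-month column is marked for both arms.

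**Purpose of the 4-month weighing.** Under Intervention group, at 4 months "parents will be invited for a second session and advice on weaning and feedback on" the baby's growth will be given. Under Control group: "The control group will be offered the same number of contacts with facilitators (attention control"). That section mentions no weighing.

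**Detection rule.** Under Eliciting adverse events: "Baby weight measurements might reveal underweight", defined as weight below the 0.4th centile, or weight faltering, defined as "crossing down through ≥2 weight centile lines". Neither the visits that count nor the earlier weight from which a fall is measured is stated.

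**Handling.** Under Reporting adverse events, all adverse events go into the case report form. Underweight and faltering, there called incidental findings, are reviewed by paediatricians and reported to the GP, usually leading to more frequent weight monitoring when there are no other symptoms.

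**The concern.** The intervention aims to lower formula intake, so too little weight gain is the obvious physical harm to look for. The article calls the risks negligible but promises to elicit adverse events actively. The underweight and faltering findings are the direct evidence on that claim.

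That evidence is gathered with unequal intensity. An infant in the intervention arm who dips at 4 months and recovers by 6 months is found; the same infant in the control arm is not found by the study. An excess in the intervention arm could then be a product of the extra weighing, or a real excess could be explained away as extra surveillance. Neither reading could be excluded from the counts.

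There is a second-order effect. A 4-month finding can lead to closer monitoring in one arm only, and this could influence later weights.

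**Working it through.** The article states no rate of underweight or faltering, so there is no figure of its own to reproduce.

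**1. Count the looks (Table 1).** Intervention: baseline, 4, 6 and 12 months = 4 weighings, 3 after baseline. Control: baseline, 6 and 12 months = 3 weighings, 2 after baseline.

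**2. Direction.** Let A be the event that an infant is flagged on the common weighings, and B the event that the infant is flagged only because the 4-month weight exists. With no treatment effect, the control probability is P(A) and the intervention probability is P(A) + P(B), with P(B) ≥ 0. The ratio is 1 + P(B)/P(A), which cannot be below 1. This needs no assumption about growth.

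**3. Size, by simulation under no effect.** There were 1,000,000 infants per scenario, with the same weight-SDS process in both arms.

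- From the article: the weighing schedule; the 0.4th-centile limit; a band width of 0.67 SDS (Growth), so two bands = 2 × 0.67 = 1.34 SDS; a mean gain of 0.65 SDS (Sample size calculation), used as upward drift in half the scenarios; 300 infants per arm, the lower end of the recruitment target.
- Assumed, because the article does not give them: baseline at 2 months; correlation r between SDS values 2 months apart of 0.75, 0.85 or 0.92, with correlation r^√(months apart/2) at other spacings; 20%, 40%, 50% and 100% of the drift reached by 2, 4, 6 and 12 months.
- Flag: SDS below the 0.4th centile at any weighing, or a fall of at least 1.34 SDS from any earlier weight, including birth.

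| r | Drift by 12 months | Control | Intervention | Ratio | Extra per 300 |
|---|---|---|---|---|---|
| 0.75 | 0 | 23.8% | 29.6% | 1.24 | 17.3 |
| 0.75 | 0.65 | 11.8% | 16.4% | 1.39 | 13.8 |
| 0.85 | 0 | 12.3% | 15.0% | 1.22 | 8.1 |
| 0.85 | 0.65 | 3.9% | 5.4% | 1.39 | 4.5 |
| 0.92 | 0 | 3.6% | 4.2% | 1.17 | 1.8 |
| 0.92 | 0.65 | 0.6% | 0.8% | 1.26 | 0.5 |

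Ratios and extras come from unrounded shares. For r = 0.85 without drift: 0.150/0.123 = 1.22, and 300 × (0.150 − 0.123) = 8.1.

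**4. Sensitivity to the reference weight.** If a fall is measured from birth weight only, the excess in faltering is smaller. At r = 0.85 without drift it is 7.18% against 8.03%, ratio 0.0803/0.0718 = 1.12. At r = 0.92 without drift it is 1.75% against 1.89%, ratio 1.08.

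**5. Sensitivity to the definition.** The 1.34 SDS rule is a stand-in. The article speaks of crossing two or more centile lines, and a fall of little more than one band (0.67 SDS) can do that. A separate run used birth correlations of 0.60–0.70, 0.55–0.65 and 0.50–0.60 at 4, 6 and 12 months, a 4-to-6-month correlation of 0.92 and linear drift. It gave ratios of 1.12 to 1.33 with the 1.34 rule and 1.11 to 1.31 with actual line crossing. The literal definition flags more infants in both arms, so the absolute numbers in the table are indicative only.

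**6. After the fix.** If both arms are judged on the same weighings, P(B) drops out and the expected null ratio is 1.00.

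**The case against.** The strongest reply is that the article plans no between-arm comparison of faltering. Its listed comparisons cover growth, crossing of one centile band, diet, temperament and sleep, psychological mediators, parents' BMI, acceptability and costs. Where the authors want a comparison for adverse effects, as for temperament and sleep, they say so. The safety section can be read purely as case-finding for the individual baby. Which visits enter a safety table is commonly settled in an analysis plan, which is not shown here, and visit dates would allow the restriction after data collection.

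Much of this stands. A reader might infer that a planned test of faltering is biased; no such test is described. A reader might also infer that every such finding is formally classed as an adverse event. The heading of the section suggests it, but the reporting section calls these incidental findings and gives them their own route. And the 4-month weighing has an open purpose, growth feedback, so it is not a slip.

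What does not stand is that nothing here needs settling. The article itself states both the unequal schedule and a detection rule with no restriction on visits. Together they distort any tabulation of these findings by arm, however informal, on the main physical risk of the intervention. An unseen plan may restrict the comparison; nothing shown does.

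**Conclusion.** The point holds for any by-arm summary of underweight or weight faltering, and only for that. The asymmetry is explicit in Table 1, and the direction of the expected distortion follows without modelling.

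The size is uncertain. A null ratio of roughly 1.1 to 1.4, and an excess of under 1 to about 17 infants per 300, rest on assumed correlations, drift and a 1.34 SDS rule, none of which the article fixes for this purpose. Other assumptions could produce a larger ratio, but the documents supply no inputs that would support quoting an excess of a half or more.

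Two stronger readings should be set aside. First, a reader might infer that the intervention arm is bound to show more cases. That is true only in expectation; chance could reverse it in one trial. Second, a reader might infer that the main result is compromised. The primary outcome runs from birth to 12 months, and the 6- and 12-month growth comparisons likewise use weights taken in both arms, so they are not directly affected. The only possible route is indirect, through closer monitoring after a 4-month finding, and the documents give no means of sizing it.

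**What to change.** Add to Eliciting adverse events and Reporting adverse events that any between-arm summary of underweight or weight faltering uses only the weights scheduled in both arms: baseline, 6 and 12 months, with birth weight as the available earlier reference. In that summary the 4-month weight should serve neither as a detection point nor as the earlier weight from which a later fall is counted. List findings first made at the intervention-only 4-month weighing separately, outside the comparison.

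Clinical review and GP reporting of every finding, at whatever visit, stay as written.

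The cost is one or two sentences and one extra table row, with no new data or visits. The limitation is that the separate list cannot undo any effect of follow-up triggered by a 4-month finding in one arm. It does show how many infants were exposed to it.

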## Abbreviations

ALSPAC: Avon Longitudinal Study of Parents and Children
BMI: body mass index
DH: Department of Health
DINO: Diet In Nutrients Out
DNSIYC: Diet and Nutrition Survey of Infants and Young Children
GCP: good clinical practice
GP: general practice
NCMP: National Childhood Measurement Programme
NHS: National Health Service
MRC: Medical Research Council
MRC HNR: Medical Research Council Human Nutrition Research Unit
SACN: Scientific Advisory Committee on Nutrition
SCT: Social Cognitive Theory
SDS: standard deviation score (number of standard deviations above or below the 50^th^ percentile)
VAS: visual analogue scale, measure of health status on a scale of 1–100
WHO: World Health Organisation

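### The safety section assesses change in parental anxiety with a scale the protocol elsewhere calls quality of life or health status, although an anxiety inventory is scheduled at the same visits

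*Protocol article*

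**What the plan says.** The protocol article, under Assessment of safety (Eliciting adverse events), identifies the harm: "A potential unintended consequence of the Baby Milk intervention could be increased anxiety for the parent(s"). It assigns the instrument in the next sentence: "Changes in anxiety levels will be assessed using the EuroQoL Visual Analogue Scale (VAS"). The main caregiver fills in this scale at the first visit and again at 6 months. The section attaches an action to that instrument: "A drop in score of >30 points at 6 months will initiate a follow-up phone call by the study team".

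Three other places describe the same scale differently:

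- Table 1, footnote e: "Quality of Life: EuroQol Visual Analogue Scale and Short Form 8".
- Questionnaires: the scale is paired with the SF-8 as the measure of the parent's quality of life.
- Abbreviations: "visual analogue scale, measure of health status", scored from 1 to 100.

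Table 1 also has a separate row for maternal anxiety. Footnote f gives its instrument as a "Short State Anxiety Inventory". The row is marked for both groups at baseline and 6 months.

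**The concern.** Anxiety is the only harm to parents that the safety section names, so the instrument assigned to it should be the one the trial uses to measure anxiety. As written, it is a general self-rating of health. A caregiver could become considerably more anxious while rating her health much as before. Another could rate her health far lower because of a physical illness, with no change in anxiety. If the section is followed literally, the assessment of this harm relies on a score that responds to many things besides anxiety, while a specific measure taken at the same visits is not mentioned.

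This is not a detail left to a fuller document. The article states an instrument, and that statement conflicts with its own table, questionnaire section and abbreviation list.

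**Working it through.** No formula applies; the check is whether the sections agree on which instrument measures anxiety and when.

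| Place in the protocol article | Instrument | Labelled as | Visits |
|---|---|---|---|
| Eliciting adverse events | EuroQoL VAS | change in anxiety | baseline, 6 months |
| Table 1, quality-of-life row and footnote e | EuroQoL VAS with Short Form 8 | maternal quality of life | baseline, 6 and 12 months |
| Questionnaires | EuroQoL VAS with SF-8 | parent's quality of life | not stated for this scale |
| Abbreviations | VAS | health status, 1 to 100 | not applicable |
| Table 1, anxiety row and footnote f | short state anxiety inventory | maternal anxiety | baseline, 6 months |

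1. **Instrument.** Of the four places that describe the VAS, only the safety section treats it as a measure of anxiety. The other three agree with one another that it measures quality of life or health status.
2. **Timing.** The safety assessment needs baseline and 6 months. The anxiety inventory is scheduled at exactly those two visits, in both groups, so availability of data does not explain the choice of the VAS.
3. **Cross-reference.** The inventory appears only in Table 1 and its footnote. The safety section does not mention it, and no action is tied to it.
4. **Other text.** Nothing else in the article reconciles the two descriptions. The other adverse effects it mentions (underweight, weight faltering, infant temperament and sleep) concern the baby.
5. **Size.** The article gives no mean or standard deviation for the VAS, no figures for the inventory and no correlation between them. How many anxious caregivers the VAS would miss, or how many it would flag for other reasons, cannot be calculated from the document.

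**The case against.** The strongest reply is that the trial does collect a specific anxiety measure in both groups at both visits, so a randomised comparison of anxiety remains possible. That is correct. The fault lies in the safety section's assignment, not in data collection.

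A second reply is that a large fall in self-rated health may partly reflect distress, and that the VAS is not the only channel: adverse events are to be actively elicited and both groups have a help-line. This also stands in part. The VAS is non-specific rather than irrelevant, and the other channels soften the consequence. None of them measures anxiety specifically, however, and a proxy is hard to defend when the direct measure is taken at the same visits.

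Three stronger readings are tempting, and the document does not support them:

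- **That the trial does not measure anxiety, or would report its absence from VAS data.** Table 1 contradicts the first. On the second, the safety section describes a prompt for an individual phone call; it plans no between-group VAS comparison and makes no reporting claim.
- **That the loss of sensitivity can be quantified.** Any figure would need an assumed correlation between the two scales and a flagging rule, such as a worst percentage, that is not the protocol's. Its rule is an absolute fall of more than 30 points.
- **That the trigger excludes a meaningful group of caregivers.** On a scale starting at 1, someone at 31 or below at baseline can fall by at most 31 − 1 = 30 and so cannot meet the rule. The arithmetic is right, but no baseline distribution is given, so its practical weight is unknown; any trigger based on a fall has such a floor.

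**Conclusion.** The contradiction is real and unresolved in the article. The safety section assesses the one harm to parents that it names with a scale that the rest of the protocol classes as quality of life or health status, and it passes over the anxiety inventory scheduled at the same visits. The consequence is a non-specific safety assessment of anxiety, not an absence of anxiety data.

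Severity is moderate. The primary outcome, randomisation, sample size and main analysis are untouched, and no numerical size can be attached. The conclusion rests on the article's own labels for the two instruments and on the visit schedule in Table 1; it needs no assumption about how the two scores are related.

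**What to change.** In Eliciting adverse events, state that change in maternal anxiety from baseline to 6 months is assessed with the state anxiety inventory already listed in Table 1, and describe the EuroQoL VAS only as a quality-of-life measure, in line with Table 1 and Questionnaires.

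The follow-up-call rule is a matter of clinical management. The clinical investigators should reconcile it with Table 1, Questionnaires and Abbreviations; no instrument or cut-off for it is proposed here. How anxiety is compared between groups may be left to the analysis plan.

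The cost is a change of wording and the scoring of a questionnaire that is already collected. No visit, measurement or participant burden is added.
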